## Abstract

**Background:**

Kenyan women experience a high burden from breast and cervical cancers. Screening can result in earlier diagnosis, but its uptake is extremely low. The proportion of women up to date with screenings per guidelines is low, implying that interactions between providers and women are reduced.

**Objective:**

We will test complementary strategies in community and clinic settings that can improve community–clinic linkages and address multilevel barriers. We aim to conduct randomized trials to compare a C3Link (cancer community–clinic linkage) program with enhanced usual care. We will (1) conduct a cluster randomized trial to assess the short-term and longer-term impact of the C3Link package of strategies, (2) use a mixed methods approach to assess multilevel implementation outcomes, and (3) perform cost-effectiveness and return on investment analysis.

**Methods:**

We will create the C3Link package aimed at increasing breast and cervical cancer screenings, and adopt a study design to assess and evaluate sustainability in 3 counties: Machakos, Nakuru, and Nyeri. Three noncontiguous communities for each of the 9 study clinics (3 per county) will be randomly assigned to one of the study arms using the R (R Foundation) program. The intensity of the strategies varies from low (awareness campaign for the enhanced usual care arm), to medium (C3Link Core arm with study community health worker–led group education and study community health worker–embedded clinic teams enhanced with practice facilitation), and to high (C3Link Plus arm with C3Link Core and a predetermined sequence of individual strategies). Women aged 30 to 55 years (1 per household) will be eligible to participate and could select a support person for inclusion. Trained data collectors will conduct surveys for women, their support persons, and from providers in the clinics using questionnaires, tracking tools, and focus group discussion guides. We will collect data and conduct interviews and focus groups to identify underlying moderating factors associated with the successful implementation of strategies. We will use implementation science methods to evaluate the effectiveness, implementation outcomes, and cost-effectiveness of the C3Link program compared with the enhanced usual care.

**Results:**

This study was funded in July 2022, received institutional review board approvals in November 2022 (United States) and June 2023 (Kenya). It was registered on ClinicalTrials.gov in September 2024. Enrollment of this study’s cohort began in September 2024 and was concluded in November 2024. We began implementing the interventions in 2025 and will report on our primary end points on screening uptake and follow-up in 2027 based on 24-month follow-up data.

**Conclusions:**

The C3Link Program is expected to yield better screening and follow-up outcomes than the control but will require more resources. Incremental cost-effectiveness of each strategy in the outlined sequence will be determined.

## Introduction

### Background

In Kenya, breast and cervical cancers are the most commonly diagnosed cancers and the leading causes of mortality among women [1]. Most of these cancers are diagnosed at a late stage: 60% of breast cancers and 53% of cervical cancers are diagnosed in stages III or IV [2-5]. In contrast, about two-thirds of breast cancers are identified at an early stage in the United States [6]. Treating late-stage cancers is more challenging, often with a poor prognosis, which results in high levels of premature mortality and morbidity in Kenya [7]. For example, the mortality-to-incidence ratio ([mortality rate/incidence rate]*100), for breast cancer in Kenya is 48% compared to 12.7% in the United States and 14.9% in the United Kingdom [1,8,9]. For cervical cancer, it is 53.9% in Kenya, compared to 34.9% in the United States and 26.7% in the United Kingdom [1,8,9]. Notably, the incidence rate for breast cancer in the United States and the United Kingdom is more than double that in Kenya, and the incidence rate for cervical cancer in Kenya is more than 5 times that in the United States and the United Kingdom [1,8,9]. Mitigation measures in the United Kingdom include human papillomavirus (HPV)–based screening—a high-performance test—and mammography at personalized intervals, hence early detection and interventions for cervical and breast cancer, respectively, and HPV vaccination for cervical cancer for both boys and girls younger than 10 years [10,11].

There is abundant evidence that screening results in an earlier stage of diagnosis and, in fact, that screening can prevent cervical cancer [12-16]. National estimates for Kenya, of women who have ever received screening, are 14% and 48% for breast and cervical cancer, respectively, where the 48% in cervical cancer includes all methods, while HPV testing accounts for less than 6% [5,17]. The proportion of women up-to-date with screenings within intervals recommended by guidelines is likely much lower [18]. This low level of engagement in the screening process also means that health care providers have limited opportunity to educate women to identify cancer symptoms, which can further facilitate early diagnosis. Early detection of cancer can occur by increasing screening uptake and improving knowledge of symptoms.

Breast cancer screening guidelines for women in Kenya previously included mammography from level 4 health facilities (subcounty hospitals to national referral hospitals), and clinical breast examinations (CBE) from level 2 facilities (dispensaries and private clinics) onward, with referrals for screening mammograms to higher levels as appropriate [5]. Upon testing these guidelines, logistical challenges and health system barriers were found to be a limitation; hence, the Kenya Ministry of Health (MOH) now recommends CBE at all levels with referrals to levels 4, 5, and 6 (subcounty hospitals to national referral hospitals) for diagnostic mammography (2024 guidelines), but still acknowledges mammography as the recommended screening method in the average risk population [5]. The World Health Organization and Breast Health Global Initiative support early detection by using CBE because population-wide mammography can be expensive and logistically challenging in low-resource settings. Properly done CBEs can downgrade breast cancer, improve outcomes, and reduce costs of care. The Kenya breast cancer screening guidelines recommend that women with average risk initiate screening from ages 25 years up to age 34 years with CBE every 3 years, combine CBE and ultrasound during 35‐39 years every 2 years, combine CBE and mammography during ages 40‐55 years annually, reduce this frequency to biennially during ages 56‐74 years, then determine continuation based on individual factors. Women at higher risk are to receive intensive screening and/or genetic counseling [5].

The rationale for cervical cancer screening in Kenya is to achieve sufficient coverage based on the WHO’s Cervical Cancer Elimination Strategy’s recommendation (achieve 70% of women screened by a high-performance test (HPV test), aiming to screen every woman aged 30‐49 years nationwide at least twice [17]. HPV testing also has the advantage of self-sample collection at level 1 (community level) of the health system, which can be aided by community health workers (CHWs) and is deemed culturally acceptable, reducing embarrassment and stigma associated with pelvic examinations. Population-wide cervical cancer screening targets women aged 25‐49 years and recommends that women 30 years of age or younger receive Papanicolaou tests and those older receive HPV tests; 5-yearly for those uninfected with HIV and 3-yearly for those infected with HIV [17]. Multistakeholder efforts have seen marked improvement of screened women aged 25‐49 years from 5% in 2018 to 48% in 2024 [5]. Even with this improvement, Kenya still falls short of the 70% WHO target.

Kenya’s Cancer Screening Guidelines recommend CBEs and mammograms for breast cancer screening, and ultrasound when recommended by health care providers, and the National Cervical Cancer Elimination Plan recommends HPV DNA testing for cervical cancer screening [5,17]. To spearhead screening access, the government has invested in screening by installing mammography machines and updated laboratory services in each county. The screening infrastructure is substantially underused even though CBEs for breast and visual inspection with acetic acid/visual inspection with Lugol’s iodine for cervical cancer screenings are offered free of charge at many public health facilities, which eliminates a key barrier related to cost [19]. Our extensive formative research, supported by other published studies, revealed that, although women generally know about screening, they have a limited understanding of the available cancer screening services [20-25]. A key gap is the lack of linkages between women in the community and clinics where services are provided, which perpetuates the situation in which screening services are available, but there is no demand for the services.

At the individual level, women lack knowledge of their risk factors and the role of screening as a prevention and early detection tool [4,21,22]. These factors, along with fear of the tests, limit their personal agency to seek screening [6,7,26]. At the interpersonal level, social norms that perpetuate fatalism, cancer stigma, and gender roles in decision-making also discourage care-seeking behavior [26-29]. At the structural level, barriers include provider knowledge, discomfort discussing sensitive topics [21,30], provider stigma, and inadequate communication of test results. For example, more than one-third of women did not receive their test results in a screening pilot study in Nyeri County [31].

The theoretical framework used, based on the socioecological model [32], is presented in Figure 1. Drawing on the literature and prior studies already cited, we will create the C3Link (cancer community–clinic linkage) multicomponent strategies targeted at barriers at the individual, interpersonal, and structural levels. These strategies are guided by the COM-B (Capability, Opportunity, and Motivation–Behavior) change model [3], in which capacity (CHW-facilitated cancer knowledge and risk assessment), opportunity (availability of high-quality screenings and confidence in the health care system), and motivation (self-efficacy, peer support, and care-seeking behavior) [4,6,7,12-16,26,33-35] interact to facilitate behavior change. Given the extremely low levels of cancer screening in Kenya and the importance of screening to reduce premature mortality, community stakeholders deemed it unethical to use the “current standard of care” as the comparison arm. We will, therefore, vary the intensity of the strategies from low (awareness campaign for the enhanced standard of care), to medium (C3Link Core with CHW-led group education and CHW-embedded clinic teams enhanced with practice facilitation), and to high (C3Link Plus with C3Link Core and a predetermined sequence of individual strategies). We will test the hypothesis that the C3Link (Core or Plus) combination of CHW-led community strategies for women (individual level) and their families (interpersonal level), along with health system practice facilitation (structural level), will increase cancer screening compared to the enhanced standard of care. Furthermore, we anticipate that CLink Plus will improve screening outcomes the most but will also require the most resources. Assessment of implementation outcomes, using the Proctor framework [36] and incremental cost-effectiveness analysis, will guide the selection of optimal strategies.

**Figure 1. F1:**
[figure not shown]
Conceptual framework for creating linkages and addressing barriers to reduce cancer mortality; C3Link study. C3Link: cancer community–clinic linkage.

### Objectives

This cluster randomized controlled trial aims to assess the short-term and longer-term impact of a package of strategies (C3Link Program), assess multilevel implementation outcomes, and perform cost-effectiveness and return on investment analysis to support scale-up of effective approaches and strategies.

Kenya has expended substantial resources to improve their screening infrastructure, but this investment continues to be underused due to logistical and health system barriers. A key gap, as described in the background section, that perpetuates the low breast and cervical cancer screening rates in Kenya is the lack of community–clinic linkages, anticipated or perceived stigma, and reduced self-efficacy to undergo screening. The planned assessment of the C3Link packages can provide the evidence to overcome barriers and to justify further investment in cancer screening, which is essential to scale up the Kenyan guidelines’ recommended services and inform policies under universal health coverage, which is being adopted across Kenya. Our main objective is to develop and test complementary strategies in community and clinic settings that can improve C3Linkages and address multilevel barriers.

We will create the C3Link package of implementation strategies that will include CHW-led strategies in the community and practice facilitation in the clinic setting.

For the community setting, there is growing evidence on the important role CHWs play in addressing individual and interpersonal barriers to improve knowledge and encourage women to seek medical care [12,13,33,37]. In Kenya, pilot studies in Meru and Nyeri counties have shown that CHWs can facilitate uptake of cancer screening [14,31]. We will use the lessons learned to develop 2 packages of strategies, the C3Link Core and C3Link Plus models. For C3Link Core, CHWs will deliver group education sessions to women and families (male partner or other support person), which is an evidence-based, low-cost strategy to promote cancer screening [15,16,34,35,38]. In our formative research, we found that many women were comfortable discussing issues related to fear and misinformation in individual rather than group settings [19-21]. Therefore, we hypothesize that group education sessions will motivate some women to screen, but others will require an individual-level strategy, or a combination of multiple individual-level strategies [39], to seek screening. To optimize available resources and adopt a tiered process through which only women who require multiple strategies are offered them, C3Link Plus will include the C3Link group education sessions and then add on individual evidence-based strategies [40-42] that increase in resource intensity in a sequential order, targeting women who remain unscreened at 1-month intervals. Women who remain unscreened after group sessions will first receive one-on-one education, followed by motivational interviewing, and, finally, navigation to address specific barriers.

For the clinic setting, the C3Link Core and Plus will use practice facilitation in clinics to foster team-based care with CHWs from the community embedded within the clinic teams to build optimal C3Linkages and communication channels. Practice facilitation is an implementation strategy that has been used successfully in varied settings to build health care workforce capacity and support changes to improve outcomes in health care facilities [43-46]. CHWs serving as team members in the clinic setting can return test results to women and cocreate optimal processes in screening clinics to support completion of follow-up recommendations. We will also provide education to health care providers to improve communication and reduce any stigmatizing behaviors. Furthermore, based on feedback from women in our study communities, we have adopted a holistic women-centered approach (supported by over 80% of the women [47]) to increase uptake of cancer screenings. The community education will include general wellness and disease prevention, and wellness examinations (hypertension and diabetes screening) will be offered during screening clinic visits and annually.

We will supplement the infrastructure investments already in place by providing additional training on cancer screening procedures. Through the practice facilitation process, we will implement a learning collaborative that will offer peer-to-peer consultations to improve screening capacity. In prior discrete choice experiments, which are a quantitative stated preference method to systematically assess attributes women value most in deciding to undergo cancer screening, the competency of the provider was the key attribute [47,48].

The main aim of this study is to conduct randomized trials to compare a C3Link program with enhanced usual care. This study aims to (1) conduct a cluster randomized trial to assess short-term (intervention phase) and longer-term impact (maintenance phase) of the C3Link package of strategies, (2) use a mixed methods approach to assess multilevel implementation outcomes, and (3) perform cost-effectiveness and return on investment analysis to support scale-up of effective approaches and strategies.

### Hypothesis Testing

We will test the following hypotheses: (1) women from communities with more evidence-based strategies (C3Link Plus followed by C3Link Core and then enhanced standard of care) will have progressively higher cancer screening uptake (completion of recommended breast and cervical screenings); (2) women from communities with C3Link Core or Plus strategies will have higher follow-up compliance with supplemental or diagnostic follow-up referrals and initiation of cancer treatment than women in the enhanced standard of care; (3) women from C3Link Plus communities will have higher completion of recommended repeat breast and cervical cancer screenings than women from C3Link Core or enhanced standard-of-care communities; and (4) women from communities that receive C3Link Core or Plus strategies will have improved self-efficacy, social support, and knowledge of cancer risk factors compared to women in the enhanced standard-of-care communities.

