### Study Design and Sample Size Determination

The sample size was determined using standard parameters (*α*=.05, 2-sided tests), based on the primary end point and allowing for the detection of a 15 percentage point improvement in the primary end point, our minimum threshold to consider the C3Link package of strategies to be successful. For the enhanced standard-of-care arm, given the current low level of screening, we estimated the screening uptake for both cancers to be about 15% at the 24-month follow-up (end of intervention phase). With a sample size of 100 in each of the 9 communities in the trial arms (for a total of 2700 women, and each woman will select 1 family member or support person), we will be able to detect a 15% difference with over 80% power, even after accounting for up to 20% attrition at 24 months. We selected a screening uptake of at least 30% in either the C3Link Core or Plus arm on the basis of prior study results [62,63]. We estimate that the interclass correlation coefficient would be in the range of 0.03 to 0.05 because interclass correlation coefficients for binary data are typically quite small, especially when screening uptake is very low [64]. Furthermore, we anticipate that the C3Link Plus arm would achieve a higher uptake than the C3Link Core arm, and we would be able to detect any difference of 15 percentage points between this study’s arms (ie, screening uptake of 15%, 30%, and 45% in the enhanced standard-of-care, C3Link Core, and C3Link Plus arms, respectively) with over 90% power. In each community, we will select study participants, 1 woman per household, using the Kish method [65], with eligibility remaining the same as previously stated. We will oversample by 10% to account for participants who cannot be contacted, refuse to participate, or are no longer eligible. The C3Link study cluster randomization is presented in Figure 2.

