### Recruitment

The 3 communities per study clinic will be randomly assigned to one of the following study arms: C3Link Core, C3Link Plus, or enhanced standard of care. Trained study data collectors and study CHWs will visit households in the selected communities with the help of county CHWs (promoters). They will visit households in selected communities and enroll eligible women. Women will be eligible to participate if they are 30 to 55 years of age to capture most cases of persistent HPV infections (lower age limit) and those within the peak age groups of breast cancer incidence rate in Kenya (higher age limit). These women will be due to receive both breast and cervical cancer screening during this study’s intervention phase based on Kenyan guideline recommendations, not experiencing breast or cervical cancer symptoms, not pregnant, fluent in a study language (English, Kiswahili, Kamba, Kalenjin, and Kikuyu), and have plans to remain in the community for at least 2 years. We will include women who meet the inclusion criteria (1 per household using the Kish method) [65].

The study CHWs will administer a short survey to all women to assess eligibility for this study. The data collectors will administer the baseline survey to women who will give voluntary informed consent to participate. Each enrolled woman will be allowed to select a support person (spouse or community member) older than 18 years of age—the legal age for consent for health research in Kenya, with help from their CHW if needed. Selecting a support person will be voluntary. Study CHWs will administer a support person eligibility checklist tool before data collectors administer the support person baseline survey to those who give voluntary informed consent.

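### The stated power of over 90% for any 15-point difference is not met for C3Link Plus v Core over most of the plan's own ICC range (about 76-90%), and showing both adjacent steps has about 64-87%

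*Protocol article*

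**What the plan says.** The Hypothesis Testing section of the Protocol article lists four hypotheses. The first concerns screening uptake, the primary end point, and is worded as an ordering: "C3Link Plus followed by C3Link Core and then enhanced standard of care) will have progressively higher cancer screening uptake".

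Study Design and Sample Size Determination makes two power statements.

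- **Over 80%.** This is for a 15-point difference, "even after accounting for up to 20% attrition at 24 months". It is anchored on control: "we estimated the screening uptake for both cancers to be about 15% at the 24-month follow-up", with success set at 30% or more in either C3Link arm.
- **Over 90%.** This is for uptake of 15%, 30% and 45% in control, Core and Plus: "we would be able to detect any difference of 15 percentage points between this study’s arms".

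The design is given as "With a sample size of 100 in each of the 9 communities in the trial arms (for a total of 2700 women". The assumed correlation is stated as "interclass correlation coefficient would be in the range of 0.03 to 0.05". Tests are two-sided at 0.05. The Recruitment section describes allocation within clinic: "The 3 communities per study clinic will be randomly assigned to one of the following study arms".

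The second power statement does not say whether it means each pair, one pair or an overall test. No power is printed for showing both adjacent steps. The Data Analysis section names generalized estimating equations across the three groups and no rule for declaring the ordering.

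**The concern.** At 15%, 30% and 45% there are exactly two 15-point differences: Core v control and Plus v Core. The natural reading of the second power statement is that each can be detected with more than 90% power. The variance of a proportion rises towards 50%, so 30% v 45% is harder to separate than 15% v 30% with the same number of women. A figure that fits the first pair need not fit the second.

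The same two differences are the two steps of hypothesis 1. Showing both is harder than showing either one, and a reader who sees the ordered scenario beside a figure above 90% gets no warning of that.

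What is at stake is the Plus v Core step. The Discussion says the trial will give the incremental cost-effectiveness of each strategy in the sequence to guide policy, and Plus is the arm expected to need the most resources. Whether Plus adds to Core is the weaker of the two comparisons.

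**Working it through.** **Inputs, all from Study Design and Sample Size Determination.** There are k = 9 communities per arm, with m = 100 women per community, or 80 after 20% attrition. ICC is 0.03 to 0.05, alpha is 0.05 two-sided (critical value 1.960), and uptake is 15%, 30%, 45%. Arms are treated as independent, because no between-clinic variance is given.

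**Formulas.**
- Design effect: DE = 1 + (m − 1) × ICC.
- Effective number per arm: n = 9m / DE.
- SE of a difference: √{[p₁(1 − p₁) + p₂(1 − p₂)] / n}.
- Power for one pair: Φ(0.15/SE − 1.960).
- The values of p(1 − p) are 0.1275, 0.2100 and 0.2475. They sum to 0.3375 for Core v control and 0.4575 for Plus v Core.

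**Example, ICC 0.03, m = 80.** DE = 1 + 79 × 0.03 = 3.37 and n = 720/3.37 = 213.6.
- Core v control: SE = √(0.3375/213.6) = 0.0397; power = Φ(3.774 − 1.960) = 96.5%.
- Plus v Core: SE = √(0.4575/213.6) = 0.0463; power = Φ(3.242 − 1.960) = 90.0%.

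**Example, ICC 0.05, m = 80.** DE = 4.95 and n = 720/4.95 = 145.5.
- Core v control: SE = 0.0482; power = Φ(3.114 − 1.960) = 87.6%.
- Plus v Core: SE = 0.0561; power = Φ(2.675 − 1.960) = 76.3%.

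**Both steps.** The Core estimate enters the two contrasts with opposite sign. Their correlation is −0.2100 / √(0.3375 × 0.4575) = −0.534. Joint power is the bivariate normal probability that both exceed 1.960.

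| Women analysed per community | ICC | Core v control | Plus v Core | Both steps |
|---|---|---|---|---|
| 80 | 0.03 | 96.5% | 90.0% | 86.5% |
| 80 | 0.04 | 92.5% | 83.1% | 75.6% |
| 80 | 0.05 | 87.6% | 76.3% | 64.2% |
| 100 | 0.03 | 97.3% | 91.6% | 88.9% |
| 100 | 0.04 | 93.6% | 84.8% | 78.4% |
| 100 | 0.05 | 88.8% | 77.9% | 67.0% |

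**Against the plan's figures.**
- Over 80% for 15% v 30% reproduces at every ICC, with and without attrition.
- Over 90% for any 15-point difference does not. With attrition, Plus v Core only just reaches 90% at ICC 0.03 and falls below it above that. Without attrition it stays above 90% up to an ICC of about 0.032. Core v control falls below 90% above an ICC of about 0.045 with attrition.
- No point in the stated ICC range gives 90% for both steps.

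**Sensitivity.**
- A version of the test with a slightly different variance formula gives 86.9-96.3% for Core v control and 75.5-89.6% for Plus v Core after attrition, so the conclusion does not depend on that choice.
- One-sided testing at 0.05 does not rescue the figure: 84.4% for Plus v Core at ICC 0.05 with attrition.
- Had each pair exactly 90% power, both steps together would have about 80%. Correcting the pairwise figure therefore does not by itself give the power for the ordering.

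**The case against.** Four points can be made on the other side.

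**The document does not attach the 90% to hypothesis 1.** This stands. A reader might infer that the plan claims over 90% power for the ordering. It does not: the sentence speaks of 15-point differences between arms and never mentions the hypothesis. The error is in the pairwise figure; the joint figure is simply not given.

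**The rule that both steps must be significant is an inference.** This also stands. It is drawn from the word progressively, and the article fixes no test for the ordering. The rule may sit in an analysis plan not shown here, so its absence is not a fault. An overall two-degree-of-freedom test, or a trend test driven by the 30-point gap between Plus and control, has over 99% power. Neither would by itself show that Plus exceeds Core or that each 15-point difference has been detected.

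**The trial was sized on a different target.** The sample rests on a 15-point gain over control in either C3Link arm. The Introduction likewise words the test as Core or Plus against enhanced standard of care, and only anticipates that Plus does best. That target is met, so it would be wrong to infer that the trial is too small for its sizing target.

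**Clinic blocking is ignored.** Each clinic contributes one community to each arm, and an analysis that uses this could remove part of the between-community variance. As an assumption, if 25% of it were removed, the power for both steps would be about 93% at ICC 0.03 and 79% at 0.05; if 50%, about 98% and 91%. The article gives no clinic variance and claims no such gain, so this qualifies the figures without rescuing the printed one. For the same reason I do not rely on an unpaired cluster-level t test with 16 degrees of freedom, which gives about 55-80% for both steps after attrition. It ignores the blocking and is not the planned analysis.

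**Conclusion.** The concern holds as a correction to a printed figure. Under the section's own inputs, two-sided 0.05, the normal approximation and no credit for blocking, power after 20% attrition is about 88-97% for Core v control and about 76-90% for Plus v Core. The statement of over 90% for any 15-point difference is up to about 14 points too high for Plus v Core and about 2 points too high for Core v control, both at ICC 0.05.

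If hypothesis 1 is to be claimed step by step, the power is about 64-87%, or 67-89% without attrition. At ICC 0.05 such a claim would fail about one time in three (100 − 64.2 = 35.8%) even if 15%, 30% and 45% were exactly true. About half of that gap from 90% comes from the weak Plus v Core step (90 − 76.3 = 13.7 points) and the rest from requiring both steps (76.3 − 64.2 = 12.1 points).

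The incremental cost-effectiveness analysis is a matter of estimation and does not need two significant tests. The consequence for it is imprecision in the Plus v Core difference.

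**What to change.** In Study Design and Sample Size Determination:

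- Replace the single figure of over 90% with power by named pair and ICC. After 20% attrition these are 96.5%, 92.5% and 87.6% for Core v control, and 90.0%, 83.1% and 76.3% for Plus v Core, at ICC 0.03, 0.04 and 0.05.
- Add one sentence: the power to show both adjacent steps is about 64-87% under these assumptions, and blocking by clinic could raise it.
- Do not leave over 90% attached to Plus v Core.
- Do not claim that Plus exceeds Core from an overall or trend test alone.

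The statement of over 80% for 15% v 30% stays. No change to the sample size is needed and no particular testing sequence is required. The cost is a few lines of text before the primary analysis planned for early 2027. The only drawback is a less favourable power statement for Plus v Core.
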